#### Notification Data Analysis

Notification data from RMHC sensors will be analyzed for patterns and trends of clients’ activity in the home. Data will be downloaded from the technology provider database quarterly and analyzed by the researchers. Exploratory pattern analysis will include reviewing each individual’s pattern of notifications. In addition, data will be aggregated to examine patterns that might inform understanding of the population (eg, common issues such as medication delay, sleep/wake patterns). These data will provide broader insights about daily patterns of older adults living in their home that may lead to other interventions to support home care service planning.

#### Economic Analysis

An economic analysis will be undertaken by the study health economists to examine health care costs from the perspective of the health system. The objective of the economic analysis is to compare the costs associated the RMHC model against those of the usual publicly funded home care received by control group participants. The economic analysis will be conducted using primary data from the study and secondary data from the administrative databases (from provincial and regional health authority databases—ie, the Ontario Institute for Clinical Evaluative Sciences, Health Data Nova Scotia ) for costs associated with older adult health service use (ie, hospitalization, emergency room visits, and home care services) along with costs associated with home care delivery. The costs of the delivery (service fees for installation and monthly maintenance) of the RM intervention will also be included. With data on health service use, costs for each older adult participant will be calculated by multiplying the individual resource use (from the study and home care database) with unit costs (from provincial standard costing sources such as the Schedule of Benefits [36-39]). We will analyze the total cost variable as a dependent variable, using regression, to estimate the difference in expected health care cost between the RMHC model of care and usual care. The intervention variable will be the primary independent variable, and the model will adjust for previously mentioned potential confounding variables. Ordinary least squares model produces unbiased estimates even if the data are skewed [40]. Subgroup analyses (eg, by sites, by sex) will be explored.

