## Introduction

Older adult Canadians (aged 65 years and older) experience significant chronic disease challenges [1], yet most older adults want to remain at home even if their health conditions challenge their ability to live independently [2].

There is evidence that “...when home care is appropriately managed and properly integrated into the health care system, it can improve the health and well-being of many seniors and their families and reduce the costs of care in hospitals and long-term care facilities” [3]. However, evidence suggests that there is room for improvement in current home care service delivery. Recent studies showed that 25% of Canadian older adults receive only partial home care services and experience unmet home care needs that create a cascade of events resulting in deterioration of older adults’ health and the need for institutionalized care [2,4]. Older adults want to be assured that their health care needs can and will be effectively addressed [5].

Part of the challenge in caring for older adults in their homes lies in providing suitable home care services and ensuring that older adults can safely follow their established treatment plan (eg, adherence to medication protocol). From a health care perspective, we have yet to feel the full effects of the impact of older adult health care challenges [6]. The transfer of health care services to the home setting is a strategic move intended to accommodate the desire of many older adults to remain at home and minimize acute care costs [7]. Yet home care resources are tenuous due, in part, to challenges in attracting and sustaining a work force (eg, nurses) that will be paid lower wages than in the hospital sector [3,5].

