## Methods

### Study Design

This 4-year study is an unblinded pragmatic randomized controlled trial (PRCT) with two parallel arms [19-22]. PRCTs are well-suited to supporting decisions about complex interventions tested in the real world when comparing with usual care [23,24]. The objective of the study is to examine the effectiveness of the RMHC versus usual home care in maintaining the client in their place of residence and delaying or preventing admission to higher levels of care such as hospitalization or long-term care.

This study builds on the findings of previous pilot studies conducted in the provinces of New Brunswick, Alberta, Nova Scotia, and British Columbia. The primary aims of this study are to test whether (1) RM along with usual home care (the intervention) versus usual home care alone (control) allow older adults with complex care needs to remain in their home longer and delay or avoid admission to higher levels of care (eg, hospitalization and long-term care), (2) intervention is cost effective, and (3) intervention will improve the quality of life for clients and family/friend caregivers. The primary outcome for this study is the occurrence of and time to events such as terminal admission to hospital awaiting admission to long-term care and direct admission to long-term care. The secondary outcomes for this study are (1) health care costs, (2) client functional status and quality of life in the home, (3) family/friend caregiver stress, and (4) family/friend caregiver functional health status.

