#### Intervention

Clients will receive RMHC in addition to usual home care services. The intervention group will receive passive RM sensors to detect a combination of the following behaviors/movement patterns: medication administration, opening refrigerator/cupboards, getting in and out of bed, movement in the bathroom, use of exit doors, movement detection, and for observation (cameras). The study technology partner, CareLink Advantage (www.carelinkadvantage.ca), will cover the equipment and monitoring costs. Once enrolled in the study, clients and their family/friend caregivers will have a home visit by the technology partner (or designate). They will receive written and verbal overview of the various RM options. Based on the assessment by the technology partner along with client and family/friend caregiver preferences, the RM options will be customized and implemented. The intervention will be offered to the client for 12 months at which time the client will be transitioned to usual care. Notifications of atypical events (eg, missed medication, atypical length of time in bed) will be sent to the family/friend caregiver via either email, text message, or phone call. Action, based on the notification, may include a telephone call to prompt the client or check on the client’s safety, deployment of assistive home care supports, or emergency action (eg, ambulance). During the study, researchers will not receive any notifications. However, at the end of the study notification patterns and trends will be analyzed.

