#### Health Care Costs

Health care cost to the Ministries of Health (ie, hospitalization, emergency room visits, and home care services) will be captured from administrative databases (from provincial and regional authority databases).

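### The cost outcome leaves out long-term care, the service the trial aims to avoid, so the cost difference is biased against the intervention if it works

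*Protocol article*

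**What the plan says.** The protocol article defines the cost outcome in two places. Under Health Care Costs it is "Health care cost to the Ministries of Health (ie, hospitalization, emergency room visits, and home care services", taken from administrative databases. Under Economic Analysis the same three services return as "costs associated with older adult health service use (ie, hospitalization, emergency room visits, and home care services". That section adds home care delivery costs and then the intervention: "The costs of the delivery (service fees for installation and monthly maintenance) of the RM intervention will also be included". Neither section names long-term care.

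The Economic Analysis section says it will "examine health care costs from the perspective of the health system". Its one stated estimate comes from a regression of total cost, "to estimate the difference in expected health care cost between the RMHC model of care and usual care".

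Elsewhere, Study Design lists among the aims to test whether "2) intervention is cost effective". Study Design and Measures both make direct entry to long-term care part of the primary outcome, alongside terminal hospital admission. Selection Criteria restricts enrolment to clients judged likely to enter long-term care within 12 months.

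**The concern.** The trial enrols people expected to enter long-term care and asks whether the intervention keeps them at home, but the cost outcome does not price the alternative to staying at home.

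The result is an asymmetry. A client who enters long-term care stops generating home care cost, and nothing is charged for the care that replaces it. A client kept at home goes on generating home care cost and, in the intervention arm, monitoring fees. Those home costs are real and belong in the comparison. The error is that their counterpart is missing. If the intervention reduces long-term care use, the missing cost is larger in the control arm, and the estimated difference is too high by that amount. Covariate adjustment and a larger sample do not help, because the dependent variable itself is incomplete.

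A second gap is related. The aim speaks of cost effectiveness, while the stated analysis compares costs only and does not relate them to any effect. Both gaps affect a result that the article's conclusions address to decision-makers.

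**Working it through.** **The plan's own figures.** The article gives no cost figure and no unit cost. The only usable inputs are the institutionalization proportions in Sample Size Calculation: 0.41 (control) and 0.27 (intervention). They do appear to be the operative planning values. A two-sided continuity-corrected comparison at 80% power with 2:1 allocation needs 146 intervention clients. Allowing for 10% dropout gives 161 (146 × 1.1) or 163 (146 / 0.9), against the stated 160.

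**The bias as a formula.** Let L be the monthly public cost of long-term care, and m_C and m_I the mean months spent there per client in each arm. Then

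full difference = counted difference + L × (m_I − m_C),

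so the counted difference (intervention minus control) is too high by L × (m_C − m_I). This is zero if the intervention does not change long-term care use, and positive if it reduces it.

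**Institutional time.** Assumptions not in the article: the two proportions apply at 12 months, hazards are constant, and there are no deaths.

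- Control hazard: −ln(0.59)/12 = 0.0440 per month. Mean months at home in the year: 0.41/0.0440 = 9.32. Institutional: 12 − 9.32 = 2.68.
- Intervention hazard: −ln(0.73)/12 = 0.0262 per month. Mean months at home: 0.27/0.0262 = 10.30. Institutional: 12 − 10.30 = 1.70.
- Difference: 0.97 month per client (from unrounded values).

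As a check on the timing assumption, spreading the same events evenly over the year gives (0.41 − 0.27) × 6 = 0.84 month.

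**In money.** With an assumed L of $3,000 to $6,000 per month, 0.97 × L is about $2,900 to $5,800 per client. This treats all institutional time as uncosted. Hospital time is in the cost list, so the figure is a ceiling under these assumptions. If half the institutional time were in hospital, it would be about $1,450 to $2,900.

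**Does the sign change?** This depends on unit costs that the article does not give. Two assumed sets of monthly costs, with the monitoring fee charged for the 10.30 months at home:

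| Home care | Long-term care | Monitoring | Counted difference | With long-term care |
|---|---|---|---|---|
| 1,000 | 4,000 | 100 | +2,000 | −1,882 |
| 1,000 | 2,000 | 300 | +4,059 | +2,118 |

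The sign reverses in the first set and not in the second. Neither includes any difference in hospital or emergency cost, which the planned analysis would count.

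**The case against.** **The list may not be closed.** The article sometimes uses *ie* loosely. The Introduction uses it for a list of incidents that trigger a notification, and the Intervention section later gives an event outside that list. The Economic Analysis section also speaks of a total cost and a health-system perspective. This leaves room for the authors to have intended long-term care. But the same three services appear in both definitions, the second adds other items without adding this one, and an analyst who follows the text would leave long-term care out.

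**The main saving may still be counted.** Hospital and emergency costs are included, and so is time in hospital awaiting a long-term care place, one of the two primary-outcome routes. The article does not give the split between routes. This stands: it is why 0.97 month is a ceiling, and why the size of the bias is uncertain although its direction is not.

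**Stronger readings that a reader might infer, and that the article does not support:**

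- *A cost-saving intervention will be reported as cost-increasing.* This is possible but not shown. It depends on unit costs, the public share of long-term care cost and hospital savings, none of which the article gives.
- *The error grows over the five further years of service-use data.* The Results section describes data collection only. No economic horizon is stated, Quantitative Data plans analyses at 6 and 12 months, and the intervention ends at 12 months. Carrying the hazards forward has no basis.
- *Donated equipment is left unpriced.* The technology partner "will cover the equipment and monitoring costs", yet the plan does charge service fees. Whether those fees include equipment is not stated.
- *The least squares standard errors are wrong.* The article claims only unbiasedness under skew and names no variance estimator, a detail normally left to an analysis plan.
- *Long-term care savings are this trial's stated rationale.* The Introduction's phrase "reduce the costs of care in hospitals and long-term care facilities" quotes an outside source on home care in general.

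**Conclusion.** The point holds as a fault in the cost definition as written. Both definitions omit long-term care, while the primary outcome, the stated perspective and the cost-effectiveness aim all require it. If the intervention lowers long-term care use, the estimated cost difference is biased against it. If it does not, the omission causes no systematic bias.

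The size is at most about 0.97 institutional month per client, or about $2,900 to $5,800 at an assumed $3,000 to $6,000 per month. This rests on a 12-month horizon for 0.41 and 0.27, constant hazards, no deaths and no institutional time in hospital. A change of sign cannot be claimed or excluded from the article.

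Health care cost is a secondary outcome. The primary analysis, sample size and randomization are unaffected.

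**What to change.** In both Health Care Costs and Economic Analysis, add publicly funded long-term care days multiplied by a unit cost, in both arms, so that each client's cost is complete to 12 months wherever the client lives. If the authors already intend this, the two lists should say so.

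Then bring the aim and the analysis into line. Either relate the cost difference to the primary outcome already being collected, for example as incremental cost per institutionalization avoided, or restate the second aim as a cost comparison.

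The cost is small. Health-number linkage and long-term care admission data are already planned, so this is one more data element in the administrative request and a little more analysis. Sample size, randomization and participant burden do not change.

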#### Phase I: Survey Data Collection

Researchers will meet with clients and family/friend caregivers in the home of the client or by phone at baseline, 6 months, and 12 months to collect data. It is expected the interviews will last no more than one hour. Paper format questionnaires including standardized instruments and researcher-developed questions will be used to collect data at each time point (see Measures). Data on reasons for leaving the study will also be collected. A demographic form will be used to collect basic demographics including age, education, sex, marital status, income, and individuals’ provincial health insurance number. The provincial health insurance number will be used for data linkage to provincial administrative health care databases in order to conduct the economic evaluation.

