### Data Analysis

#### Quantitative Data

Quantitative data will be analyzed at baseline, with subsequent analysis of primary/secondary outcomes at 6 months and 12 months. Using SPSS Statistics version 25 (IBM Corp) statistical software, descriptive statistics will provide a profile of study participants including demographics, current diagnoses, length of home care before the study, and model of care (RMHC versus usual care). The provisional effect of the intervention on the primary outcome will be tested using a prospective chi-square test of independence (continuity-corrected) between the experimental and control groups (Fisher exact test). Repeated measures analysis of variance will measure mean differences between groups on continuous variables. We intend to use multivariate survival analyses methods using a relevant time dependent outcome based on the ability to accurately track the main event of interest (ie, institutionalization) [24]. We will conduct within and between province analyses on secondary outcomes. Subgroup analyses will include examining differences based on sex (male/female) in both clients and family/friend caregivers.

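### As written, the cost regression does not adjust for health care cost before randomization and does not name province as a covariate, so the cost difference may be less precise than it need be

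*Protocol article*

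**What the plan says.** The Economic Analysis section sets out the cost model: "We will analyze the total cost variable as a dependent variable, using regression, to estimate the difference in expected health care cost". The intervention is the main independent variable. On the other covariates, the section says only that "the model will adjust for previously mentioned potential confounding variables". The estimator is ordinary least squares, justified by the remark that "Ordinary least squares model produces unbiased estimates even if the data are skewed".

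Two earlier places come closest to a list of baseline variables:

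- Quantitative Data: "descriptive statistics will provide a profile of study participants including demographics, current diagnoses, length of home care before the study, and model of care".
- Phase I: Survey Data Collection: "A demographic form will be used to collect basic demographics including age, education, sex, marital status, income, and individuals’ provincial health insurance number". The insurance number "will be used for data linkage to provincial administrative health care databases in order to conduct the economic evaluation".

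Neither is presented as an adjustment set.

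Province is mentioned three times in relevant ways. The abstract names Ontario and Nova Scotia as two geographic strata, Quantitative Data plans within- and between-province analyses of secondary outcomes, and Economic Analysis offers exploratory subgroups by site.

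**The concern.** Health care cost is the first secondary outcome, and cost-effectiveness is the second of the aims listed under Study Design. The cost regression is therefore the analysis that answers a stated aim.

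In a randomized comparison, baseline covariates in a cost model serve mainly to explain outcome variation and so tighten the interval. Calling them confounders hides that purpose. A client's own past cost is a natural candidate for this role, because it is measured on the same scale and with the same components as the outcome. The article points back to variables already mentioned, and past cost is not among them. Province is mentioned, but never as a term in this model, although the unit costs come from provincial sources.

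What is at stake is the width of the interval around the cost difference. The validity of the comparison is not in question.

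**Working it through.** **Does any reading of the back-reference include prior cost?**

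1. *Strict reading: variables already called confounders.* None exists, so the set is empty and prior cost is outside it.
2. *Profile reading: the descriptive list in Quantitative Data, without the arm.* This gives demographics, current diagnoses and length of home care before the study. Prior cost is not there. Length of home care is a baseline variable that may partly stand in for past home care use.
3. *Widest reading: everything named earlier, including the demographic form and the Measures section.* Cost appears there only as an outcome. Pre-randomization cost is still absent.

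Province is outside readings 1 and 2. Under reading 3 it is mentioned, but as a stratum and a subgroup factor.

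**The plan's own figure.** The article gives no standard deviation, correlation or precision target for cost. Its only size is 160 + 320 = 480, set on the primary outcome. That reproduces. For 0.27 against 0.41, two-sided alpha 0.05, 80% power, 2:1 allocation and a continuity correction, the result is 146 + 292 = 438. Allowing for 10% dropout gives 163 + 326 = 489 (dividing by 0.9) or 161 + 322 = 483 (multiplying by 1.1). For cost, 480 supplies only the arm sizes.

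**Unadjusted precision, in units of the cost SD.**

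SE = SD × √(1/160 + 1/320) = 0.0968 SD

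95% half-width = 1.96 × 0.0968 = 0.190 SD

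With 10% dropout (144 and 288), the SE is 0.102 SD and the half-width 0.200 SD. The ratios below do not change.

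**Adding prior cost.** Let r be the correlation between prior and follow-up cost. The SE is multiplied by √(1 − r²), and the equivalent sample size by 1/(1 − r²). The article does not give r, so the values are assumed.

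| Assumed r | √(1 − r²) | Interval narrower by | 95% half-width (SD) | 1/(1 − r²) | Equivalent total N |
|---|---|---|---|---|---|
| 0.3 | 0.954 | 5% | 0.181 | 1.10 | 527 |
| 0.4 | 0.917 | 8% | 0.174 | 1.19 | 571 |
| 0.5 | 0.866 | 13% | 0.164 | 1.33 | 640 |
| 0.6 | 0.800 | 20% | 0.152 | 1.56 | 750 |

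The table compares adjustment for prior cost with no adjustment at all. The plan does adjust for something. The relevant r is then the partial correlation given those covariates, which would ordinarily be smaller. The table should be read as an upper bound on the gain.

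**Adding province alone.** Suppose mean cost differs between provinces by d within-province SDs and a share q of clients is in one province. Then R² = q(1 − q)d² / [1 + q(1 − q)d²], and the SE is multiplied by √(1 − R²). Both q and d are assumed.

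- q = 0.5, d = 0.1: R² = 0.0025, factor 0.999.
- q = 0.5, d = 0.5: R² = 0.0588, factor 0.970.
- q = 0.3, d = 0.5: R² = 0.0499, factor 0.975.

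The gain is about 0.1% to 3%.

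**The case against.** The strongest reply is that a journal article condenses a longer document, and a covariate list is the kind of detail left to the full protocol or analysis plan. The loose back-reference may be a remnant of that condensing. This stands as far as the missing list goes: the absence of an itemized set is not held against the article. It does not dispose of prior cost, because the phrase points to variables already mentioned and prior cost is not one of them.

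A second reply is that the profile in Quantitative Data, without the arm, is a sensible baseline adjustment set. That is plausible, since the arm enters the cost model separately. It supports the view that the plan already adjusts for something, and so reduces the gain available.

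A third is that the size rests on assumed correlations and that no look-back period is stated. Both are true, and both are carried into the verdict.

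A reader might infer more than the text supports:

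- *That the cost difference is biased.* Randomization protects it. Leaving out a prognostic baseline variable does not bias the difference in mean cost.
- *That functional status or caregiver burden at 6 or 12 months would enter as a confounder.* The wording does not rule this out, but no section proposes it, and the most plausible reading consists of baseline characteristics.
- *That province is ignored.* It is a stratum, the basis of between-province analyses of secondary outcomes, and a site subgroup for cost. Only its use as a covariate in the main cost model is unstated.

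**Conclusion.** The point holds as a precision improvement. It does not show an error or a bias. The cost model refers to variables already mentioned, no variable is labelled a confounder, and cost before randomization is mentioned nowhere, so the model as written does not adjust for it.

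Under an assumed correlation of 0.3 to 0.6, including it would narrow the interval by at most about 5% to 20%, and by less to the extent that the planned covariates overlap with it. Province alone would probably add 3% or less. It is worth naming because it is a declared stratum and unit costs are provincial, more than for its effect on the standard error.

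The conclusion assumes that the planned linkage can reach back before enrolment. That is a reasonable inference from the use of the health insurance number, but the article does not say so. The primary outcome is not affected.

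**What to change.** In Economic Analysis, replace the back-reference with a prespecified list of covariates, all measured before randomization. Include province and the client's health care cost in the 12 months before randomization, the latter built from the same components as the outcome (hospitalization, emergency room visits, home care services) in the same linked databases. Other baseline variables, such as age, sex and length of home care before the study, can be kept if the team intends them. Fixing the list before outcome data are analyzed also removes any later choice over covariates, which is useful in an unblinded trial.

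The cost is a change of wording, a few degrees of freedom against a target of 480 participants, and 12 months of look-back in the administrative data. The article states no look-back period, so the data-access request needs to cover it explicitly. Recruitment and participant contact are unchanged.
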